## Abstract

*Introduction*: Water accounts for about 75% of brain mass. Cognitive performances and mood may be impaired by hypohydration and improved by water supplementation. Two surveys conducted in China demonstrated that a large proportion of adults and children drank less fluid than the amounts recommended by the Chinese Nutrition Society. The association between hypohydration and cognitive performance has not been reported in China. The purpose of this study is to explore the effect of water supplementation on cognitive performances and mood among male college students in Cangzhou, China. *Methods and Analysis*: A randomized controlled trial is designed to test the hypothesis. A total of 68 male college students aged 18–25 years will be recruited and randomly assigned into water-supplementation group (WS group, *n* = 34) and no water-supplementation group (NW group, *n* = 34) after an overnight fasting, i.e., without eating foods and drinking fluid for 12 h. The first morning urine will be collected to determine urine osmolality on the water supplementation day. Cognitive performances and mood will be performed before water supplementation by researchers with questionnaire. Subjects in the WS group will drink 400 mL purified water within 5 min, while those in NW group will not drink any fluid. One hour later, urine will be collected and urine osmolality, cognitive performances and mood will be measured again. Mixed model of repeated measures ANOVA will be used to investigate the effect of water supplementation on cognitive performances. The study would provide information about the benefit of water supplementation on cognitive performances. *Ethics and Dissemination*: The study protocol is reviewed and approved by the Ethical Review Committee of the Chinese Nutrition Society. Ethical approval project identification code is CNS-2015-001. Results will be published according to the CONSORT statement and will be reported in peer-reviewed journals. *Trial registration*: Chinese clinical trial registry. Identifier: ChiCTR-IOR-15007020. Registry name “The effect of hydration on cognitive performance”.

## 1. Introduction

Water is the main component of human body and is crucial for human survival. Water has functions of participating in metabolism, modulating normal osmotic pressure and maintaining electrolyte balance [1]. In addition, heat generated in the process of metabolism can be absorbed by water so as to avoid rapid increase in body temperature and there is also an important way to maintain a constant body temperature through evaporating sweat from skin surface [2]. Furthermore, water accounts for about 75% of brain mass. It is indicated that hypohydration induced by deficiency of total body water [3] may impair cognitive performances and mood, water supplementation may improve cognitive performances and mood. 

A few studies found the associations between hypohydration and cognitive performances. Cian et al. indicated that heat stress and exercise-induced hypohydration impaired perceptive discrimination, psycho-motor skills, and short-term memory and had adverse effect on fatigue [4,5]. Lieberman et al. revealed that military exercise in heat had adverse effect on cognitive performances and mood [6]. Baker et al. demonstrated that vigilance-related attention was impaired by hypohydration after a basketball game in the heat [7]. D’anci et al. showed that digit span performance, vigilance attention, choice reaction decrements resulting from mild hypohydration induced by exercise and fluid restriction [8]. Ganio et al. showed that the mild hypohydration induced by combination of exercise and diuretics impaired vigilance and working memory, and increased tension/anxiety and fatigue [9]. Armstrong et al. also reported that hypohydration in females can increased perception of task difficulty and degraded mood [10]. However, some studies obtained inconsistent results. Sharma et al., Bandelow et al. and Ely et al. showed that no statistically significant change in cognitive performances was observed under hypohydration induce by heat stress and exercise [11,12,13]. In most studies, a state of hypohydration was induced through heat stress, physical activity, or diuretics, and so on. However, heat stress and physical activity themselves may have impacts on cognitive performances. Hypohydration state in free-living life was studied less, which need further studies.

Another important issue is whether water supplementation have beneficial effects of on cognitive performances. Rogers et al. showed that cognitive performances improved depending on thirst after water supplementation [14]. Edmonds et al. also revealed that subjective thirst moderated the positive effect of water supplementation on speed of responding [15]. In another study of Edmonds et al., it was reported that water supplementation had effect on cognitive performances, no matter with either expectancies or mood [16,17,18]. Fadda et al. suggested a beneficial effect of water supplementation on short-term memory. Benefer et al. reported that water intake were associated with post-exercise cognitive performance (short-term memory) [19]. However, paradoxically, Neave et al. and Benton et al. demonstrated that water supplementation had no effect on cognitive performances. Backes et al. demonstrated that there was a lack of facilitation of cognition in the 500 mL water supplementation condition other than in the 150 mL condition [20]. Different amount of water supplementation, different types of cognitive performances and different duration after water supplementation may cause conflict results, which need more studies with appropriate study design.

In China, there are no studies about the effects of hypohydration state and water supplementation on cognitive performances. Only two surveys about fluid intake were conducted. In 2009, Ma et al. conducted a fluid intake survey among 1483 adults from four cities in China, it was found that approximately 32% of the subjects drank less water than the 1200 mL/day recommended by the Chinese Nutrition Society [21]. In another survey among 5868 primary and middle school students from the same four cities [22], it was reported that nearly two-thirds of the subjects drank less than the recommended amount. The results of two above-mentioned surveys imply that large proportion of Chinese residents may be in a hypohydration state, and their cognitive may be impaired. One hypothesis is that hypohydration state will impair cognitive performances and mood. Another hypothesis is that water supplementation will improve hydration state, cognitive performances and mood. The objectives of this study are, firstly, to evaluate the effect of water supplementation on cognitive performances, secondly, to explore its effect on mood among college students, and finally, to raise the awareness of keeping adequate hydration state and promote water-related education in China.

## 2. Methods and Analysis

### 2.1. Study Hypothesis

One hypothesis is that hypohydration state will impair cognitive performances and mood. Another hypothesis is that water supplementation will improve hydration state, cognitive performances and mood.

### 2.2. Study Design and Assignment of Interventions

This is a randomized controlled trial. After being encoded according to student ID, recruited subjects will be randomly assigned to the water-supplementation group (WS group, 34) and no water-supplementation group (NW group, 34) using random number table to generate random sequence by investigators. Measurements on blood pressure, blood glucose, urine osmolality, urine sodium concentration, urine specific gravity, test of subjective sensation of satiety, hunger, sleepiness and thirst, mood and cognitive performances will be performed before and after water supplementation (Figure 1). All items from the World Health Organization Trial Registration Data Set are shown in Table 1.

### 2.3. Sample Size Calculation

The variable used for the calculation of sample size is digit span. Digit span is used to assess short-term memory. It was reported that the average values of digit span for subjects with water supplementation and without water supplementation were 10.5 and 11.5, respectively [18]. The values was taken as reference for our study and 80% power is set. SAS 9.2 (SAS Institute Inc., Cary, NC, USA) is used to calculate the sample size. Only male students will be studied, for the reason that women’s menstrual cycle may have impacts on urine indicators and cognitive performances. In addition, 10% drop-out rate is taken into account. Eventually, a total of 68 subjects will be needed. 

### 2.4. Subjects

Subjects will be recruited from freshman and sophomore years in one college in Cangzhou, Hebei province of China, by the method of online recruitment advertisements. Inclusion criteria: aged between 18 and 25 years; male; being in healthy state. Exclusion criteria: aged <18 years or >25 years; smoking, habitual alcohol (>20 g/day) consumption [23] or intensive physical exercise, or with the diseases of cognitive disorder, diabetes, gastrointestinal tract disease, oral disease, kidney disease, other chronic diseases and metabolic diseases. 

### 2.5. Ethics

The study protocol has been approved by the Ethical Review Committee of the Chinese Nutrition Society. Ethical approval project identification code is CNS-2015-001. The study will be conducted according to the guidelines of the Declaration of Helsinki. Prior to the study, all subjects will read and sign the informed consent form.

### 2.6. Study Procedure

A total of nine days will be needed to complete the study.

#### 2.6.1. Assessment of Total Drinking Fluid

In order to assess the daily total drinking fluid, all subjects will complete a self-administrative 7-day 24-h fluid intake record questionnaire after training, during the period of day 1 to day 7. The type and the amounts of drinking fluid for each time will be recorded and measured by a cup to the nearest of 10 mL. Subjects will pour fluid into the cups to measure the amount before they drink the bottle water, sugar sweetened beverages, milk, etc. The method of 7-day 24-h fluid intake record has been used in previous studies and has been proved to be reliable [16,17,18]. 

#### 2.6.2. Assessment of Fluid from Foods

All foods eaten by subjects will be weighed for three consecutive days during the seven days (including two weekdays and one weekend day) to calculate the daily fluid intake from foods. 

#### 2.6.3. Temperature and Humidity

The temperature and humidity of indoor and outdoor at the study site will be recorded at 10:00 a.m., 2:00 p.m. and 8:00 p.m. in the nine days with a temperature hygrometer.

#### 2.6.4. Assessment of Baseline Indicators

On day 8 (the day before the supplementation day), all subjects will be asked to be fast without any foods and fluid from 8:00 p.m. They will be asked to sleep before 11 PM in the evening and not urinate after sleep until getting up in the next morning to collect first urine samples. In addition, they will be asked not to do high intensity exercise before the test. Anyone who fails to meet the above requirements needs to let investigators know. The first morning urine samples in the water supplementation day will be collected in sterile disposable urine sample cup by themselves and will be tested immediately by professional lab technicians in hospital (test 1).

#### 2.6.5. Groups of Subjects

On day 9 (the water supplementation day), all subjects will be asked to arrive at the designated place at 8:00 AM. After being encoded according to student ID, subjects will be randomly assigned to the water-supplementation group (WS group, 34) and no water-supplementation group (NW group, 34) using random number table to generate random sequence. Baseline height, weight, waist circumferences, blood pressure and blood glucose will be measured (test 1: before water supplementation) following the standardized procedures. The first morning urine samples will also be collected and tested. At 8:30 AM, cognitive performances, mood and subjective sensation of satiety, hunger, sleepiness and thirst will be tested (test 1).

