#### 2.6.6. Water Supplementation

At 9:00 AM, subjects in the WS group will drink 400 mL purified water within 5 min with uniform cups in one designated place, while those in NW group will not drink any water or beverages in another designated place. Subjects in NW group will not be told the intervention of WS group. During the interval before the next test, all subjects will be asked to sit at their own seat without physical activity. They will be asked not to eat foods, drink water/beverages, and urinate. One hour after water supplementation (at 10:05 AM), blood pressure and blood glucose will be measured again in designated place (test 2: after water supplementation). Urine samples will be collected, stored and tested again (test 2). At 10:25 AM, cognitive performances, mood and subjective sensation of satiety, hunger, sleepiness and thirst will be measured again (test 2). Temperature and humidity will be recorded at 8:00 AM. During the period of the study, subjects can quit at any time for side effects, such as syncope. The study procedure is shown in Figure 2.

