### 2.7. Blinding of Data Analysis

Data analysts will analyze the data without being informed which group is water supplementation group or no water supplementation group. The names of groups will be coded as A and B. After data analysis and the finish of summary report, data analysts will be informed the group code.

The schedule of enrolment, interventions, and assessments is shown in Table 2.

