### 2.14. Cognitive performances (CP)

*Digit span forward and backward*: This will be used to assess short-term memory. A list of random numbers will be read out loudly at the rate of one per second by trained investigators. After reading a digit sequence, subjects will be asked to recall the digits in forward or backward order. The digits sequence will begin with three numbers, which should be without recognizable digit patterns on two consecutive trials of the same length. Two incorrect repetitions result in termination of the test. Digit span forward, for example, if the investigator reads ‘‘1 2 3’’, the participant will repeat ‘‘1 2 3’’. Digit span backward, for example, if the investigator reads ‘‘1 2 3’’, the participant will repeat ‘‘3 2 1’’.The number of digit without error will be counted as score respectively for digit span forward and backward [18]. Total score will be used to assess overall performances (Total score = forward score + backward score).

*Digit symbol substitution test*: This test will be used to assess digital decoding ability, visual memory, visual attention, and operating speed. It consists of nine digit-symbol pairs followed by a list of digits (total 90) (for example, 1/_, 2/⊥ ... 7/Λ, 8/X, 9/=). Subjects will be asked to write down the corresponding symbol under each digit as fast as possible within the allowed time (90 s). The number of correct symbols will be measured for score [31].

*Dose-work test*: It will be used to assess the ability of sustained attention. An Aventura Karimov table [32] will be used to evaluate the quality and quantity of dose-work. Subjects will be asked to cross the letter B behind the letter H line by line in 2 min—in an A4 format page filled with eight different letters (A, B, C, E, H, K, N, X) in a random order; total 1200 characters are on one page; each letter appear 150 times. (Reading speed (n/min) = number of already-read letters (n)/2 (min); error rate (%) = number of errors (n)/number of already-read letters (n) × 100%; mental work ability index (IMC) = number of already-read letters (n)/2 (min) × (number of letters had to be crossed − number of errors)/number of letters had to be crossed). 

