**Figure 2 ijerph-14-00966-f002:**
[figure not shown]
The study procedure. Note: H (Height); W (Weight); WC (Waist circumference); BP (Blood pressure); BG (Blood glucose); CP (Cognitive performances); POMS (Profile of Mood States); VAS (Visual Analogue Scales).

**Table 1 ijerph-14-00966-t001:** All items from the World Health Organization Trial Registration Data Set (SPIRIT checklist, item 2b).

Data Category	Information
Registration number	ChiCTR-IOR-15007020, Chinese clinical trial registry
Registration State	1008001 Prospective registration
Public title	The effect of hydration on cognitive performance
Scientific title	The effect of hydration on cognitive performance
Approval of ethic committee	Chinese Nutrition Society biomedical ethics committee
Ethical approval project identification code	CNS2015001
Date of approved by ethic committee	1 December 2015
Study type	Interventional study
Study design	Randomized parallel controlled trial
Key inclusion and exclusion criteria	Inclusion criteria: Aged between 18~25; Male; In health state, without metabolic disease, oral diseases, and so on. Exclusion criteria: Aged < 18, or age > 25; Female; With metabolic disease, oral diseases, and other diseases.
Interventions	Water supplementation
Outcomes	Urine osmotic pressure, Blood pressure, Mood, Thirsty, Cognitive performance
Collecting samples	Urine
Recruitment state	Finished
Randomization Procedure (please state who generates the random number sequence and by what method)	Primary sponsor generates random sequence with random number table.

**Table 2 ijerph-14-00966-t002:** The schedule of enrolment, interventions, and assessments.

	Enrolment	Allocation	Post-Allocation	Close-out
Timepoint	1 February 2016	14 March 2016	14 March 2016	30 March 2016
Enrolment:				
Eligibility screen	X			
Informed consent	X			
Allocation		X		
Interventions:				
Water supplementation			X	
Assessments:				
Baseline anthropometric measurements variables: blood pressure, height, weight, waist circumference	X		X	
Outcome variables: cognitive performances, mood, subjective sensation			X	X

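### Randomisation comes before the 8:30 AM baseline tests and no masking of testers is stated, so investigator-administered digit span may be given with allocation known at both tests

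*Protocol article*

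**What the plan says.** **Order of events.** Section 2.6.5 of the protocol article opens day 9 with arrival: "all subjects will be asked to arrive at the designated place at 8:00 AM". It then states that "subjects will be randomly assigned to the water-supplementation group (WS group, 34) and no water-supplementation group (NW group, 34"). Height, weight, waist, blood pressure and blood glucose come next, followed by the baseline tests: "At 8:30 AM, cognitive performances, mood and subjective sensation of satiety, hunger, sleepiness and thirst will be tested (test 1"). Under Section 2.6.6 the water is drunk at 9:00 AM and the tests are repeated later: "At 10:25 AM, cognitive performances, mood and subjective sensation of satiety, hunger, sleepiness and thirst will be measured again (test 2").

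**Masking.** Section 2.7 is the article's only section on blinding, and it concerns analysis: "Data analysts will analyze the data without being informed which group is water supplementation group" or the control group. Section 2.6.6 adds a partial safeguard for participants. No-water subjects are not told what the other group receives, and they stay in a different place.

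**Who does what.** Section 2.14 says of digit span: "A list of random numbers will be read out loudly at the rate of one per second by trained investigators". Section 2.3 makes digit span the sample-size variable. On the random sequence, Section 2.2 has it made "using random number table to generate random sequence by investigators", whereas Table 1 says "Primary sponsor generates random sequence with random number table".

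**The concern.** A baseline measured before allocation cannot be influenced by allocation. Here the baseline is measured afterwards, so its freedom from influence depends on the testers not knowing the group, and the article states nothing to secure that. The same holds at test 2, when the groups have also been in separate places.

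Digit span is the test most exposed. One person reads the digits, hears the repetition and decides whether it is wrong, and two incorrect repetitions end the test. Pace, clarity and leniency are in that person's hands. Coding the groups A and B for the analysts does nothing for scores already influenced at collection.

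At stake are the estimated effect on the variable that sizes the trial, and the assurance that differences between groups at test 1 (compared under Section 2.19) are due to chance.

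**Working it through.** **Step 1: is the order deliberate or loose wording?** Three places can be compared.

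| Place | Order given |
|---|---|
| Section 2.6.5 | arrival, randomisation, physical measures, 8:30 AM tests |
| Abstract | assignment after the overnight fast, urine, tests before water, water |
| Table 2 | outcome variables appear only under post-allocation and close-out |

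All three put allocation before the baseline tests. Section 2.6.5 gives no clock time for randomisation; 8:00 AM is the arrival time. The first step in the timetable that differs by group is the 9:00 AM drink in Section 2.6.6.

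**Step 2: who is kept from knowing the group?**

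| Party | What the article states |
|---|---|
| Data analysts | masked, groups coded A and B (2.7) |
| No-water subjects | not told the other group's intervention (2.6.6) |
| Water subjects | nothing stated; at test 2 they know they drank |
| Testers | nothing stated, either masked or unmasked |

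Investigators generate the sequence (2.2) and trained investigators give digit span (2.14). The article does not say whether these are the same people and does not separate the roles.

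**Step 3: which outcomes are exposed to the tester?** Digit span is the only test described as read aloud. Digit symbol and creativity are written, the dose-work test is crossing out letters on a page, and the mood and visual analogue scales are self-rated.

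**Step 4: how would a tester bias reach the estimate?** Section 2.19 analyses the effect on changes. Let D = (WS2 − WS1) − (NW2 − NW1), where the digits mark the test. Let b1 and b2 be the tester-induced shifts, water minus no-water, at tests 1 and 2. Then:

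expected D = true effect + (b2 − b1)

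- b1 = b2: the bias cancels.
- b1 = 0, b2 = b: D is shifted by b.
- b1 = b, b2 = 0: D is shifted by −b.

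Only the part that differs between the tests matters, and that part enters in full whatever the sample size.

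**Step 5: scale.** The planned difference is 11.5 − 10.5 = 1.0 digit (2.3). The total of 68 cannot be reproduced, because no standard deviation is given. Working back with two-sided 0.05 and 80% power, n per arm = 2 × (1.960 + 0.842)² × SD² / 1.0² ≈ 15.70 × SD². To reach 34 per arm after dividing by 0.9 and rounding up, n must be 30 (30/0.9 = 33.3), which implies an SD of about 1.36 to 1.38. That is an implied value only.

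For illustration, assume no true effect, 34 per arm, a two-sample t-test with 66 degrees of freedom and noncentrality (b2 − b1) / (SD × √(2/34)). Both the net shift and the SD of the analysed score are assumptions.

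| Net shift b2 − b1 (assumed) | SD 1.2 | SD 1.4 | SD 2.0 |
|---|---|---|---|
| 0 | 5% | 5% | 5% |
| 0.25 digits | 13.5% | 11.2% | 8.0% |
| 0.5 digits | 39.5% | 30.6% | 17.4% |

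The entries are the chance of a significant result when water has no effect. They show sensitivity and do not estimate what would happen in this trial.

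**The case against.** The strongest reply is that the article does not say testers know the allocation. It is condensed, and a fuller protocol could hold a tester roster and rules for handling the list. That stands. A reader might infer that baseline and follow-up scores are certainly taken unmasked. The text supports only that test 1 comes after allocation and that nothing stated prevents testers from knowing. The order of events, however, is stated three times and is not a detail lost in condensing.

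A reader might also infer that only the analysts are masked. That is wrong, because Section 2.6.6 withholds the water intervention from the no-water group. The safeguard limits what those subjects can expect, but it does not reach the testers or the water group.

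Digit span follows a fixed procedure (one digit per second, a three-digit start, a set stopping rule), which narrows the tester's discretion. There is also less reason for a tester to favour a group before any water is drunk, so the argument is weaker for test 1 than for test 2. Both points reduce the likely size of a bias without removing its route.

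Finally, the disagreement between Section 2.2 and Table 1 over who generates the sequence is an inconsistency in its own right. It does not show that testers were unmasked.

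**Conclusion.** The point holds as a weakness in the stated design. Randomisation precedes the baseline tests with no stated need, no tester masking is stated, and the trial's sizing variable is the one most dependent on the tester. Digit span may therefore be given with allocation known at both tests.

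The size of any bias is unknown. What can be said is structural: a bias that differs between the two tests shifts the estimated change by exactly that difference, while a constant bias cancels. The error rates tabulated above rest on assumed shifts and standard deviations. The argument applies mainly to digit span and should not be extended to the written or self-rated measures on the same grounds. Confidence is high on the order of events and moderate on the consequence, which depends on what testers actually know.

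**What to change.** - **Move randomisation.** In Section 2.6.5, place it after test 1 and immediately before 9:00 AM. Bring the abstract and Table 2 into line.
- **Separate the list from the testing.** Have one party who does not test subjects generate and hold the sequence until then. Reconcile Section 2.2 (investigators) with Table 1 (primary sponsor).
- **Roster the testers.** Use existing staff so that those giving digit span at test 2 were not in the water or no-water rooms and are not told the group. State this in Section 2.7.
- **Keep the Section 2.6.6 safeguard.** No-water subjects should still not be told the other group's intervention. For that reason, do not mix the groups before test 2 or instruct subjects not to mention drinking, since either could reveal the intervention.

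The cost is a few minutes to allocate and direct 68 subjects just before 9:00 AM, which has to fit the fixed timetable of Section 2.6.6, plus a staff roster. No visit, subject or analysis is added.
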